### Exclusion criteria

Individuals that use muscle relaxants, those with temporomandibular disorder, cerebral palsy, physical or psychiatric disorders (i.e., anxiety, persistent delusional disorder, acute and transient psychotic disorders, schizoaffective disorders and mood disorders) and those currently undergoing another treatment for bruxism will be excluded from the study.

### Inclusion criteria

Male and female children with sleep bruxism aged six to eight years with no physical or psychiatric limitations that may compromise the proposed therapies will be included. All individuals will need to have the first molars in Angle Class I and be free of dental caries. A clinical examination of tooth wear and the reports of parents/caregivers regarding tooth clenching/grinding will be used for the diagnosis of bruxism, following the criteria established by the American Academy of Sleep Medicine [1]. A questionnaire adapted from Serra Negra [28] and Manfredini et al. [29] will also be used to assist in the diagnosis of bruxism based on these two signs and symptoms (dental wear and parent’s report of tooth clenching or grinding) (Additional file 1).

### Randomisation and interventions

Randomisation will be performed using Microsoft Excel (version 2013). Seventy-six patients will be randomly allocated to the four groups. Randomisation will be in block form (groups of four patients).

Seventy-six opaque envelopes will be identified with sequential numbers (1 to 76) and each will contain information regarding the corresponding group following the established random order. The envelopes will be sealed until the time of treatment.

Patients will be allocated as follows:

Group 1 will receive low-level laser over acupoints; Group 2 will use an occlusal splint; Group 3 will receive placebo laser therapy over acupoints; and Group 4 (control group) will be composed of children without bruxism and will not receive any type of treatment. Parents/guardians will received guidance throughout the study. In G1, low-level laser (power: 70 mW; energy density: 1.675 mW/cm^2^; 12 points irradiated; 1 J per point for 20 s; 12 sessions; 12 J/session; twice a week) will be applied directly to the skin at six acupoints on each side, always by the same operator. In G2 and G3, the laser device will be positioned over the same points as in G1, but will be switched off.Group 1 – experimental (*n* = 19) – low-level laser therapy over acupoints;Group 2 –positive control (*n* = 19) – occlusal splint usage;Group 3 – control (*n* = 19) – placebo laser therapy over acupoints;Group 4 – control (*n* = 19) – children without bruxism (Additional file 2)

The child will be seated comfortably in a room without noise or sound interference and positioned with the Frankfurt plane parallel to the floor. A total of twelve sessions of LLLT will be performed at a frequency of twice per week using a laser at wavelength of 786.94 nm with a conventional tip, energy density of 25 J/cm^2^, intensity of 1.675 mW/cm^2^, power of 70 mW, 1 J (J) per point for 20 s for a total of 12 J per session. Point application will be used in direct contact with the skin (spot area: 0.04 cm^2^) following the protocol suggested by Carvalho et al. [30] and Venezian et al. [21]. The Twin Flex Evolution® device (MM Optics) will be employed. A potentiometer will be used at the onset of the study to determine the effective mean power of the equipment and therapeutic doses applied during clinical use. The points irradiated are listed below with their respective explanations:IG-4 (Hegu) - has a direct and strong influence on the face, eyes, ears, nose and mouth. It is also used to calm the mind and relieve anxiety. This point is located in the patient’s hand at the base between the thumb and index fingerF-3 (Taichong) - exerts a profound soothing effect on the mind. Its soothing action is increased when combined with IG-4.This point is located in the patient’s feet at the base between the hallux and index toe.VB-34 (Yanglingquan) - is an important point to relax the tendons whenever there are muscle contractions. This point is located in the upper distal part of gastrocnemius muscle.E-36 (Zusanli) - indicated to treat irritability, depression, insomnia, tiredness, fatigue and headache. This point is located below the patella in the lateral portion of the tibia.ID-19 (Tinggong) - indicated to treat problems in the ear region. This point is located in the anterior part of the tragusBP-6 (Sanyinjiao) - this is one of the most important points, with a broad scope of action. It has a strong soothing action on the mind and is generally used to treat insomnia. This point is located in the proximal end of the medial malleolus, the distal margin of the tibia (Additional files 3 and 4).

The patients in G3 (placebo LLLT) will receive the same treatment as those in G1, with the same equipment and a pen that emits a red guide light and a sound, but does not emit energy. After 30 days of follow up, the volunteers in this group will receive complementary treatment for the control of bruxism for ethical reasons.

For G2, the maxillary occlusal splint will be made with transparent acrylic resin and used on with upper arch with palatal and occlusal coverage. Impressions of the maxillary and mandibular arches will be made in alginate, poured in dental stone and mounted on a semi-adjustable articulator. The splint will be made in two layers of rose-colored wax and adapted to the maxillary teeth. The splint will have a thickness of 3 mm, contact with all teeth in centric relationship, distocclusion of the posterior teeth in laterality and protrusion, avoiding interferences on the swinging side with the canine guide extending from the vestibular to the lingual direction enough to prevent perforation and increase resistance to impact. An expander will also be installed so the splint will be able to accompany the growth dynamics. Following the protocol described by Hachmann et al., [20] the children will use the occlusal splint only at night for two months, with weekly adjustments of one quarter turn.

In G4 (control), children without bruxism will be evaluated. Therefore, this group will not be submitted to any bruxism treatment. This will be the control group.

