**Methods:**

The children will be randomly allocated to four groups of 19 individuals: G1 - low-level laser; G2 - occlusal splint; G3 - placebo laser; and G4 - control (without bruxism). The BTS TMJOINT electromyography will be used to determine muscle activity and a digital gnathodynamometer will be used to measure bite force. Salivary cortisol will be analysed at baseline as well as one and six months after treatment. Two-way ANOVA will be employed and complemented by Tukey’s test.

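### The plan randomises 76 children to four groups, but Group 4 is defined by not having bruxism; the scheme cannot be carried out and at most 57 children can be randomised

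*Protocol article*

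**What the plan says.** The Abstract (Methods) says: "The children will be randomly allocated to four groups of 19 individuals". It lists the control group without bruxism as the fourth of these.

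The section Randomisation and interventions repeats this and adds the block size: "Seventy-six patients will be randomly allocated to the four groups. Randomisation will be in block form (groups of four patients"). The envelopes match that count: "Seventy-six opaque envelopes will be identified with sequential numbers (1 to 76"), each holding a group assignment. The same section then defines the fourth group: "Group 4 (control group) will be composed of children without bruxism and will not receive any type of treatment".

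The Inclusion criteria admit "Male and female children with sleep bruxism aged six to eight years". No separate criteria are given for children without the condition, and nowhere does the article describe recruiting them outside the envelope sequence.

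For the analysis, the Abstract says: "Two-way ANOVA will be employed and complemented by Tukey’s test". The Statistical analyses section names ANOVA among other tests. Neither place says which groups enter the model.

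**The concern.** Membership of Groups 1 to 3 is an assigned treatment. Membership of Group 4 is a characteristic that the child already has. The allocation text treats the two alike.

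A child who meets the inclusion criterion and draws a Group 4 envelope cannot be placed there. A child without bruxism does not meet the criterion, and has no condition to treat if the envelope says laser, splint or placebo. Whoever runs the trial must therefore improvise by skipping Group 4 envelopes, redrawing, or filling those places with children found elsewhere. Each option gives a different allocation procedure, and none is the one described.

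Two things are at stake. The number reported as randomised would be wrong. And a difference between any treated group and Group 4 could be presented as randomised evidence, when it is a comparison of children with and without a disorder.

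**Working it through.** **Step 1: the plan's own counts.** From Sample size calculation: 15.75 × 1.2 = 18.9, rounded up to 19 per group, and 19 × 4 = 76. With blocks of four, 76 / 4 = 19 blocks, which is one place per group per block. These figures agree with each other, and all of them include Group 4. How 15.75 was obtained does not affect this point.

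**Step 2: who can fill each place.**

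| | Has sleep bruxism (eligible) | No bruxism |
|---|---|---|
| Groups 1 to 3 | possible | excluded by the inclusion criterion |
| Group 4 | excluded by the group's definition | possible, but no eligibility line |

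No type of child can be placed in all four groups, so random allocation across the four is impossible.

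**Step 3: what can be randomised.** Groups 1 to 3 hold 3 × 19 = 57 children. Blocks of four do not fit three equal arms (57 / 4 = 14.25 blocks). Blocks of three do (57 / 3 = 19).

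**Step 4: consequence if Group 4 enters the ANOVA (conditional).** The documents give no difference between children with and without bruxism, so I assume an offset of D standard deviations. I also assume no treatment effect (Groups 1 to 3 have equal means) and n = 16 analysable per group (15.75 rounded up).

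The four means are 0, 0, 0 and D, with overall mean D/4. Their squared deviations sum to 3(D/4)² + (3D/4)² = 0.75D². The non-centrality is therefore λ = 16 × 0.75D² = 12D². The one-way F test has 3 and 60 degrees of freedom and a 5% critical value of 2.76.

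| D | λ | Chance of a significant F (n = 16) | Same, n = 19 |
|---|---|---|---|
| 0.5 | 3.00 | 26% | 31% |
| 0.8 | 7.68 | 60% | 69% |
| 1.0 | 12.00 | 81% | 88% |

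At n = 19, 20,000 simulated trials per offset gave 30%, 69% and 89% for the four-group test. An ANOVA of Groups 1 to 3 alone stayed at about 5% whatever the offset.

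**Step 5: effect on Tukey's test.** In simulation at n = 19, with no treatment effect, four-group Tukey declared a false difference among Groups 1 to 3 in about 2.6% to 2.8% of trials, so those comparisons remain controlled. The cost is power. At n = 16 the critical studentised range is 3.74 for four groups (60 df) and 3.43 for three (45 df). The pairwise difference detectable with 80% power is 1.24 SD with Group 4 included and 1.16 SD without it.

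**The case against.** The best defence is that a reference group was probably intended. The interventions text says only that children without bruxism will be evaluated, the group list refers to an additional file not shown here, and comparing treated children with healthy ones is a legitimate question. That intent is plausible, but the article does not leave the matter open. It states a randomised count, an envelope count and a block size that all include Group 4, and the Discussion also lists Group 4 with the laser groups when it describes blinding. A fuller document could not reconcile those statements with the inclusion criterion.

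Three further objections concern the consequences, and they stand in part.

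- **A reader might infer that the efficacy analysis is a four-group ANOVA and that its result is invalid.** The text does not say so. It names a two-way ANOVA without listing the groups, and which groups enter may be settled in a document not shown. The percentages in Step 4 are for a one-way F test at one time point with an assumed offset. If the factors are group and time, a Group 4 offset that is constant over time does not by itself create a group-by-time interaction.
- **A reader might infer that the treatment comparisons are corrupted.** They are not. Tukey's test separates the pairs, and Groups 1 to 3 remain comparable with each other. The loss is the modest one in Step 5.
- **A reader might infer that concealment fails.** If Group 4 places drop out, fixed blocks of three remain and the last place in each is determined by the others (19 of 57, or 33%). That helps only someone who enrols children and knows both the block size and the earlier allocations. The statement about a single operator concerns delivery of the laser, and the envelopes are described as opaque, numbered and sealed. The article does not say who enrols.

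**Conclusion.** The point holds as a contradiction in the allocation scheme. Random allocation of 76 children to four groups cannot be carried out as written, and at most 57 children can be randomised. This follows from the article's own text and needs no assumption.

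The consequence for the analysis is conditional. If Group 4 enters the model, the overall test or the group main effect can be significant with no treatment effect: 26% to 81% for assumed offsets of 0.5 to 1 SD in a one-way test with 16 per group. This does not extend to Tukey comparisons within Groups 1 to 3, or to a group-by-time interaction under a constant offset. Failed concealment is not established.

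The allocation text should be corrected before enrolment, because it determines both the allocation list and what may be claimed as randomised evidence.

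**What to change.** 1. Randomise only the 57 children with bruxism, 1:1:1 to Groups 1 to 3, with 57 envelopes and block sizes that are multiples of three, preferably varied.
2. Recruit the 19 children without bruxism separately as a non-randomised reference group, with their own eligibility line.
3. Change the number randomised from 76 to 57 in the Abstract and in Randomisation and interventions. The total of 76 may stay as the number enrolled.
4. State that treatment inference rests on Groups 1 to 3, and label any comparison with Group 4 as non-randomised.

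The cost is revised wording and a new allocation list before enrolment, with no extra children or visits. The downside is that the headline number randomised falls by 19.

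### Group 4 is defined by the absence of bruxism, so it cannot be one of four randomised arms: only 57 of the 76 children can be randomised, and contrasts with Group 4 are observational

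*Protocol article*

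**What the plan says.** The Methods paragraph of the Abstract states: "The children will be randomly allocated to four groups of 19 individuals". It names the fourth group as a control without bruxism. The section Randomisation and interventions repeats the allocation ("Seventy-six patients will be randomly allocated to the four groups") and gives the mechanics:

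- Blocks: "Randomisation will be in block form (groups of four patients".
- Concealment: "Seventy-six opaque envelopes will be identified with sequential numbers (1 to 76) and each will contain information regarding the corresponding group".
- Opening: "The envelopes will be sealed until the time of treatment".

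The same section defines the fourth arm: "Group 4 (control group) will be composed of children without bruxism and will not receive any type of treatment". Later it adds: "In G4 (control), children without bruxism will be evaluated".

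The section Inclusion criteria opens with "Male and female children with sleep bruxism aged six to eight years" and gives no separate entry rule for children without the condition. The Discussion counts G4, together with G1 and G3, among the treatments for which participants are blinded, although G4 receives none. No section says that G4 is recruited separately or kept out of the randomisation.

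**The concern.** An envelope can assign a treatment. It cannot assign whether a child has bruxism, which is settled at diagnosis. A child who meets the inclusion criteria and draws a G4 envelope cannot belong to G4, and the article does not say what then happens to that child or to the envelope.

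Two things are at stake. First, the allocation procedure, on which a randomised trial rests, is described in a form that nobody can follow. Second, a comparison of G1, G2 or G3 with G4 sets children with bruxism against children without it. Such a comparison is observational and open to confounding, for example by age or sex. The article calls the study a randomised controlled trial, and the Abstract plans two-way ANOVA with Tukey's test without setting G4 apart. A reader could therefore give those contrasts the standing of randomised ones.

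**Working it through.** **Inputs.** Sample size calculation: 15.75 per group, increased by 20%, four groups. Randomisation and interventions: blocks of four, 76 envelopes, G4 without bruxism. Inclusion criteria: sleep bruxism required.

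**Step 1: reproduce the stated total.** 15.75 × 1.20 = 18.9, rounded up to 19 per group. 19 × 4 = 76. The figure reproduces. How 15.75 was obtained is a separate matter and plays no part here.

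**Step 2: is G4 inside the randomisation list?** The envelope count equals the four-group total, and 76 / 4 = 19 complete blocks of four. A list for G1 to G3 alone would need 19 × 3 = 57 envelopes, and blocks of four do not fit it: 57 / 4 = 14.25. The count and the block size therefore both place G4 in the list.

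**Step 3: envelopes that cannot be executed.** With equal allocation, 19 envelopes name G4, and 19 / 76 = 25%. If every child allocated meets the inclusion criteria, none of the 19 can be acted on. The number that can be randomised is 76 − 19 = 57.

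**Step 4: does the other reading rescue the text?** Assume instead that 57 children with and 19 without bruxism draw from the same list in random order. The article does not say this. The expected number with bruxism who draw G4 is 57 × 0.25 = 14.25, and the expected number without bruxism who draw G1 to G3 is 19 × 0.75 = 14.25. This reading fails too, because envelope and disease status would conflict for roughly 28 of the 76 children (14.25 + 14.25 = 28.5).

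**Step 5: contrasts affected.** Four groups give 4 × 3 / 2 = 6 pairwise contrasts. Three involve G4 (with G1, G2 and G3) and are not randomised. The other three (G1–G2, G1–G3, G2–G3) can be.

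**Step 6: what is left after correction.** 57 children in three arms of 19, for example in 57 / 3 = 19 blocks of three, plus 19 reference children: 57 + 19 = 76.

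**The case against.** The strongest reply is that this is loose wording about an ordinary healthy reference group. Inclusion rests on diagnosis, G4 children are only evaluated, and the Discussion gives the main objective as laser against splint, which does not involve G4. If each block of four holds one slot per group, striking out the G4 slots leaves a random order of G1, G2 and G3 in every block, with 19 per arm. Additional file 2, cited next to the G4 entry and not available here, may describe how G4 children enter.

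Much of this stands. A healthy reference group is legitimate, and the G1 to G3 comparisons can be randomised. But the article does not merely leave a detail out. It specifies 76 envelopes and blocks of four, and it states four-group random allocation in two places. An additional file could explain the intention but could not make those statements agree with the definition of G4.

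A reader might infer more, and the text does not support it:

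- **Staff choose among envelopes.** The article fixes sequential numbers in an established random order and gives nobody a choice. A skipped G4 envelope would lead to the next number.
- **Children without bruxism are given a laser or splint.** That needs them to be in the same draw, which the inclusion criteria do not allow for.
- **G4 has no entry rules at all.** The Angle Class I and caries requirements are worded for all individuals, and the exclusions apply to the study as a whole, so these read as covering G4. The age range, by contrast, is attached to the bruxism sentence, and no entry rule defines the absence of bruxism.
- **The main conclusion is biased.** No section draws a causal claim from a G4 contrast.

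**Conclusion.** The point holds. The four-group allocation cannot be carried out as written, because membership of G4 is fixed by diagnosis and not by an envelope. Under equal allocation, 19 of the 76 envelopes (25%) cannot be executed for a child who meets the inclusion criteria, 57 children can be randomised, and the three contrasts with G4 are observational. Equal allocation is an assumption, but it agrees with 19 per group and 19 blocks of four.

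The defect lies in the stated procedure, the stated randomised number and the standing of the G4 contrasts. It does not reach the comparisons among G1, G2 and G3, including laser against splint, which remain randomisable once G4 is off the list.

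**What to change.** 1. In the Abstract and in Randomisation and interventions, state that 57 children with bruxism are randomised 1:1:1 to G1, G2 and G3, with 57 envelopes and block sizes that are multiples of three.
2. State that 19 children without bruxism are recruited outside the randomisation as a reference group. In Inclusion criteria, give the age range and the absence of bruxism as their entry criteria, and confirm that the occlusion, caries and exclusion rules apply to them as well.
3. Describe all contrasts with G4 as non-randomised, and base efficacy conclusions on G1 to G3.
4. Correct the Discussion so that G4 is no longer counted among the blinded treatments.

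Matching G4 to the other groups on age and sex is optional and is not needed to remove the contradiction.

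The cost is wording and a new randomisation list, to be in place before the first child is allocated. The stated randomised sample falls from 76 to 57. The total of 76 and the 19 per group stay as they are, and no extra children are needed.

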## Methods

This is a protocol for a randomised, controlled, clinical trial. The project received approval from the Institutional Review Board of Nove de Julho University (Brazil) under process number 1.333.636. The participants and legal guardians will receive clarifications regarding the objectives and procedures and will sign a statement of informed consent agreeing to participate in the study.

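### The printed laser settings contradict the printed dose: 70 mW for 20 s is 1.4 J per point, not 1 J, and the protocol does not show which figure is wrong

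*Protocol article*

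**What the plan says.** The section Randomisation and interventions of the protocol article gives the laser parameters twice.

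- The paragraph on group allocation gives "power: 70 mW; energy density: 1.675 mW/cm^2^; 12 points irradiated" and then "1 J per point for 20 s; 12 sessions; 12 J/session; twice a week".
- The later paragraph on the laser procedure gives "power of 70 mW, 1 J (J) per point for 20 s for a total of 12 J per session". It adds "energy density of 25 J/cm^2^, intensity of 1.675 mW/cm^2" (the unit is per cm²) and the spot size: "Point application will be used in direct contact with the skin (spot area: 0.04 cm^2" (again cm²).

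The procedure paragraph also plans a measurement at study onset to "determine the effective mean power of the equipment and therapeutic doses applied during clinical use". It gives no measured value and does not say what changes if the measurement disagrees with the printed settings. Neither paragraph mentions pulsing, a duty cycle or an exposure shorter than 20 s.

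**The concern.** Power, time and energy are tied by one equation, so any two of them fix the third. Both paragraphs print all three, and the three do not fit together. An operator cannot both run the device at 70 mW for 20 s and deliver 1 J.

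These figures define the experimental treatment in Group 1. As they stand, a reader cannot tell whether a child in that group is meant to receive 1 J or 1.4 J per point. Anyone repeating the study could give either dose and claim to have followed the protocol. The trial report could also state a dose that was not delivered.

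**Working it through.** **Inputs**, all from Randomisation and interventions: power 70 mW = 0.070 W; time 20 s per point; 1 J per point; 12 points; 12 J per session; 12 sessions; 25 J/cm²; spot area 0.04 cm²; intensity 1.675 mW/cm².

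**Formulas.** Energy = power × time. Energy density = energy / spot area. Session energy = energy per point × number of points. Intensity = power / spot area.

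**1. The plan's dose figures agree with each other.**
- 25 J/cm² × 0.04 cm² = 1.00 J per point
- 12 points × 1 J = 12 J per session
- 12 sessions × 12 J = 144 J per course

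**2. The printed power and time give a different dose.**

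| Quantity | From 70 mW and 20 s | Stated, or implied by the stated dose | Difference |
|---|---|---|---|
| Per point | 0.070 × 20 = 1.4 J | 1 J | 0.4 J (40%) |
| Energy density | 1.4 / 0.04 = 35 J/cm² | 25 J/cm² | 10 J/cm² |
| Per session | 12 × 1.4 = 16.8 J | 12 J | 4.8 J |
| Per course | 12 × 16.8 = 201.6 J | 144 J | 57.6 J |

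**3. What would reconcile them.**
- At 70 mW, 1 J takes 1 / 0.070 = 14.3 s.
- At 20 s, 1 J needs 1 / 20 = 0.050 W = 50 mW. The document does not state this power.
- With 70 mW and 20 s both kept, the dose is 1.4 J.

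**4. Intensity.** 70 mW / 0.04 cm² = 1,750 mW/cm². The printed value is 1.675 mW/cm², and 1,750 / 1.675 ≈ 1,045, so it is about 1000 times too small. Taken literally, it gives 0.001675 × 0.04 × 20 = 0.00134 J per point. Read as 1.675 W/cm², it gives 1.675 × 0.04 = 0.067 W = 67 mW. Then 0.067 × 20 = 1.34 J, still 34% above 1 J. The group allocation paragraph also labels this figure as an energy density, although its unit is that of an intensity.

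**5. Rounding.** Power of 65 to 75 mW and time of 19.5 to 20.5 s give 0.065 × 19.5 = 1.27 J to 0.075 × 20.5 = 1.54 J. A printed whole number of 1 J could stand for 0.5 to 1.5 J, so 1.4 J might have been rounded to 1 J. The other dose figures do not allow it:
- 12 J per session: 11.5 / 12 = 0.96 J to 12.5 / 12 = 1.04 J per point
- 25 J/cm² on 0.04 cm²: 24.5 × 0.035 = 0.86 J to 25.5 × 0.045 = 1.15 J per point

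Neither range reaches 1.27 J. If 1 J is a rounded 1.4 J, then 12 J and 25 J/cm² are wrong.

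**The case against.** Three arguments on the other side deserve weight.

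First, a reader might infer that 1 J is plainly the intended dose and that the printed settings therefore over-deliver it. The document does not support that. The 12 J and 25 J/cm² may simply have been calculated from 1 J, in which case their agreement is not independent evidence. Power, time and dose per point are each printed in both paragraphs. The intensity, once its unit is corrected, points to about 67 mW and so supports the printed power. If 1.4 J was first rounded to 1 J and the other dose figures were then worked out from that, the error is in the reported dose and not in the settings. The procedure paragraph also relies on two cited protocols that are not at hand, and the 20 s may come from them. This objection stands: which figure is wrong remains open.

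Second, the onset measurement could show an effective power other than 70 mW. At 50 mW the discrepancy would vanish. This stands as a possibility, so the excess of 57.6 J per course applies only if 70 mW is really emitted for the full 20 s. It does not remove the contradiction, because the document states no 50 mW output and no rule for turning the measurement into a corrected time or dose.

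Third, a reader might infer a bias in the trial's comparisons or harm to the children. The document supports neither. The placebo device emits no energy at any setting, so a different active dose does not invalidate the comparison of Group 1 with Group 3. Nothing in the document links 1.4 J per point to a safety limit.

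**Conclusion.** The point holds as an internal contradiction in a stated treatment specification. 70 mW for 20 s is 1.4 J per point, 40% above the stated 1 J. The same gap appears as 35 against 25 J/cm² and as 16.8 against 12 J per session. No rounding makes all the printed figures agree. The separate intensity figure is about 1000 times too small and is mislabelled in one place.

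The calculation assumes continuous emission at the printed power for the whole printed time, since nothing else is described. It does not establish which of power, time or dose is wrong, or that any child would receive too much energy.

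Severity is minor. Only the delivered and reported dose of the active arm is affected. Allocation, endpoints, sample size and analysis are not.

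**What to change.** Use the effective power measured at study onset and make the figures agree in both paragraphs, in one of two ways:

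- **(a) Keep 1 J per point.** Set the exposure time to 1 J divided by the measured power: 14.3 s at 70 mW, and 20 s only if the measured power is 50 mW. The 25 J/cm² and 12 J per session then stand.
- **(b) Keep 70 mW for 20 s**, if the measurement confirms 70 mW. Restate the dose as 1.4 J per point, 35 J/cm² and 16.8 J per session.

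The choice belongs to the investigators, who know which figure was intended. State the rule next to the planned measurement.

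In both paragraphs, give the intensity as measured power / 0.04 cm² (1,750 mW/cm² at 70 mW; 1,250 mW/cm² at 50 mW). Remove the energy density label from it in the group allocation paragraph.

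The cost is a change of wording in two paragraphs, using a measurement that is already planned. Under (a) at 70 mW, irradiation per session falls from 12 × 20 = 240 s to 12 × 14.29 ≈ 171 s. Under (b) the procedure does not change.
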